# Protection of subjects

Trained study personnel will place venous accesses, administer the study drugs and collect blood samples. Subjects will be supervised by trained study personnel during the entire test sessions, backed-up by study physicians. After the test session subjects are allowed to leave only if the subjective and cardiovascular effects of MDMA have completely ceased (see 14.2.5). In the case of unexpected prolonged or severe adverse reactions subjects will remain at the CRC and are monitored as long as necessary. Subjects will be provided with the phone number of the study physician on call in case of an emergency between/after study sessions.

## Potential risks

Physical risks:

MDMA: A large series of phase I like studies have been performed using MDMA [13-16, 24, 42, 44-47, 57, 58, 67, 68, 70, 71, 74, 75, 82-91]. This considerable body of evidence indicates that the likelihood for significant toxicity from doses of MDMA such as the one to be used in the present study and in controlled settings is very low. Thus, no lasting biological or psychological injury is expected. See below for specific MDMA toxicity and monitoring. Expected adverse effects of MDMA:MDMA is expected to produce moderate acute adverse effects such as increased jaw muscle tension, dry mouth, dizziness, palpitations, tremor, nausea, headache, insomnia, and transient anxiety in more than 10% of subjects, [15, 42]. MDMA is expected to produce sequelae (1-3 days post MDMA) including difficulty concentrating, irritability, or slightly depressed mood in more than 10% of subjects [15]. No severe or serious adverse effects are expected. Duloxetine: In placebo-controlled double-blind trials in patients duloxetine (60-120 mg/day) produced nausea (20-29%), headache (20%), dry mouth (15-18%), insomnia (11-15%), fatigue (14%), dizziness (9-11%), constipation (11%), decreased appetite (8%), and sweating (6%) [63]. Adverse effects of duloxetine in healthy volunteers similary include nausea, dry mouth, insomnia, dizziness, sweating, and clinically non-significant increases in blood pressure or heart rate [25, 61, 92]. No severe or serious adverse effects are expected.

Venipunction: There is a risk for pain, bruising and thrombophlebitis.

Risk to privacy of subjects: Potential risks of data collection include breach of confidentiality. Financial risks: There is no risk of expense to the subject. Insurance coverage is provided. Travel expenses are expected to be minimal and are included in the compensation of 1000 CHF per subject.

## Monitoring of toxicity

### Safety definitions

Adverse Event (AE):

Any untoward medical occurrence in a clinical trial subject administered an investigational medicinal product (IMP) and which does not necessarily have a causal relationship with this treatment. An AE can therefore be any unfavorable and unintended sign (including an abnormal laboratory finding), symptom, or disease temporally associated with the use of an (IMP), whether or not considered related to the IMP.

Adverse Reaction (AR):

All untoward and unintended responses to an IMP judged by investigator/sponsor as having a reasonable causal relationship to the IMP. The expression reasonable causal relationship means to convey in general that there is evidence or argument to suggest a causal relationship.

Unexpected Adverse Reaction (UAR):

An AR, the nature or severity of which is not consistent with the applicable product information (e.g. investigator’s brochure for an unapproved investigational product or summary of product characteristics (SmPC) for an authorized product). When the outcome of the adverse reaction is not consistent with the applicable product information this adverse reaction should be considered as unexpected. Side effects documented in the IB or SmPC which occur in a more severe form than anticipated are also considered as being unexpected.

Serious Adverse Event (SAE) or Serious Adverse Reaction:

Any untoward medical occurrence or effect that at any dose results in death, is life-threatening, requires hospitalization, or prolongation of existing hospitalization, results in persistent or significant disability or incapacity or is a congenital anomaly or birth defect. In this context, the term life threatening refers to an event in which the trial participant was at immediate risk of death at the time of the event; it does **not** refer to an event, which might have caused death if it were more severe.

Suspected Unexpected Serious Adverse Reaction (SUSAR):

Any suspected adverse reaction related to an IMP that is both unexpected and serious.

**Causality:**

Most adverse events and adverse reactions that occur in this study, whether they are serious or not, will be expected treatment-related toxicities due to the medication used in this study. The assignment of the causality will be made by the investigator using the definitions in the table below.

| **Relationship** | **Description** |
| --- | --- |
| **Unrelated** | There is no evidence of any causal relationship. |
| **Unlikely** | There is little evidence to suggest there is a causal relationship (e.g. the event did not occur within a reasonable time after administration of the IMP). There is another reasonable explanation for the event (e.g. the participant’s clinical condition, other concomitant treatment). |
| **Possible** | There is some evidence to suggest a causal relationship (e.g. because the event occurs within a reasonable time after administration of the IMP). However, the influence of other factors may have contributed to the event (e.g. the participant’s clinical condition, other concomitant treatments). |
| **Probable** | There is evidence to suggest a causal relationship and the influence of other factors is unlikely. |
| **Definitely** | There is clear evidence to suggest a causal relationship and other possible contributing factors can be ruled out. |
| **Not assessable** | There is insufficient or incomplete evidence to make a clinical judgment of the causal relationship. |

### Documentation

All adverse events occuring after the subject has signed the informed consent will be fully recorded in the subject’s CRF. Each event will be described in detail along with start and stop dates, severity, relationship to investigational product, action taken and outcome.

### Adverse events (AE) documentation

AE events will be described and recorded on the subject’s CRF, regardless of the severity or relationship to the drug. Adverse effects are assessed by the standardized list of complaints (LC) [54]. Additional AEs are entered in the CRF at the end of the study session. AEs are also assessed 24 h after MDMA/placebo using the LC. Further, AEs are assessed before the next session 2 weeks after MDMA/placebo. AEs are rated for severity and the potential relationship to the study medications will be evaluated by the investigator according standard criteria. Subjects with AEs will be treated appropriately. Abnormal laboratory values will be repeated until normal or until the abnormality can be explained and the subject’s safety is not at risk. In cases of a medical emergency, treatment is available in house and includes the 24h-availability of the reanimation team and intensive care facilities.

### SAE and SUSAR reporting

Serious adverse events (SAE) are not expected. Should a SAE occur the PI will be informed and relationship to the study drug will be assessed by the PI using the definitions shown above (14.2.1.). Complete information concerning the SAE will be collected by the PI and documented on a standard SAE form. Any SUSAR will be reported to the IRB and Swissmedic by the PI according to guidelines and within 7 days. The PI acts as sponsor in this investigator-initiated study. Therefore no reporting to a sponsor is needed. An annual safety report will be sent to Swissmedic by the PI.

### Medical follow-up of adverse events

The investigator will ensure the subject receives medical follow-up as necessary until the condition has stabilized or returned to normal state, even if the period of the trial is over.

### Monitoring for specific toxicity

Duration of monitoring: Subjective and cardiovascular effects of MDMA last for a mean of 3.5 h and completely subside within 5-6 h [13, 42, 43, 58, 67]. Accordingly subjects are monitored for 6 h after MDMA administration. In our previous studies, that similarly evaluated interactive effects of MDMA with various pretreatments, subjects were dismissed 4 h after MDMA administration [13, 15, 68, 82]. Another interaction study used an observation time of 6 h after MDMA administration similar to the present study [43]. Only one to two subjects are tested simultaneously on the same test day.

Cardiovascular effects: Blood pressure and heart rate are measured at repeated intervals (Table 2). Closer monitoring will be implemented if blood pressure values exceed 180/120 mm Hg. Subjects will be monitored for signs of hypertensive crisis such as headache, angina pectoris or neurological deficits. Treatment of a hypertensive reaction (Psys>220 mmHg) would include administration of oxygen, lorazepam, nitroglycerin or nifedipin or/and carvedilol. In the case of angina pectoris, oxygen is given and ECG monitoring is initiated and cardiac enzymes will be measured. Subjects will remain at the CRC overnight for further observation if blood pressure is >140/95 mmHg or pulse rate is >100/min at the end of the test session at 6 PM.

Psychological effects: The effects of MDMA are mostly pleasurable. Dysphoric reactions to MDMA and moderate anxiety may occur at the onset of the MDMA effect. Such effects have always resolved within hours [42]. Unexpected severe anxiety would be treated with a benzodiazepine. Up to one third of the subjects is expected to experience slightly depressed mood including emotional irritability, lack of energy, brooding and bad dreams for up to 3 days following MDMA administration [42]. These effects will be specifically monitored using an adverse effects check list. After the test session subjects are allowed to leave only if the subjective effects of MDMA have completely ceased (VAS score “drug effect” back to predose ± 10%).

Hyperthermia: Increases in body temperature of approximately 0.5C are expected [42]. If body temperature rises by more than 1.5C appropriate treatment including hydration and cooling will be initiated [5]. Subjects will remain at the CRC overnight for further observation if body temperature has not returned to pretreatment levels ± 0.5 C at the end of the test session at 6 PM.

Dehydration/Hyperhydration: Ecstasy use has been associated with both dehydration and hyperhydration leading to hyponatremia [5]. Subjects will be encouraged to drink no less than 1 but no more than 3 l during one session. If symptoms of hyponatremia such as confusion or vomiting are present, subjects will be further examined and serum sodium levels checked.

Hepatotoxicity: Ecstasy use has been associated with idiosyncratic liver toxicity [5]. Liver enzymes will be measured at the beginning and end of the study and any pathological results will be followed up.

Neurotoxicity: Recreational use of Ecstasy has been linked to reversible neurotoxicity [93, 94], especially when the drug is taken frequently and in high doses [6, 93]. In contrast, several studies document no lasting effects of Ecstasy in moderate Ecstasy users [93, 95-97]. There is no indication that administration of MDMA in a controlled setting has any adverse effects on cognitive function [2, 89, 98]. The use of pure MDMA in controlled settings is considered safe with regard to neurotoxic effects [35, 73]. No changes in serotonin transporter density were seen using positron emission tomography and [11C]-McN5652 four weeks after MDMA administration (1.5-1.7 mg/kg) in MDMA-naïve human volunteers [99, 100]. We will administer only two single moderate doses of MDMA similar to previous clinical studies [13, 16, 17, 47, 67, 68, 82].

Abuse liability: The likelihood for future drug abuse triggered by the administration of MDMA in a controlled setting is assumed to be very low. MDMA has rewarding effects in animals and humans [74] but the risk for developing dependence is considered low when compared with other drugs of abuse [101]. In previous studies using MDMA in controlled settings, none of the participants expressed any interest in taking MDMA as a recreational drug after completing the study [15, 42]. Subjects with known risk factors for future MDMA use including depression or anxiety disorders [102] and prior drug dependence or other relevant illicit drug use [103] will be excluded from the study. Illicit drug use will also be monitored during the study using repeated urine drug screens.

## Risk-Benefit Assessment

Potential benefits: First, the present study will generate objective, scientific information about the effects of MDMA that could not be obtained with observational studies. MDMA is used non-medically by millions of people and scientific information on the pharmacological and toxicological effects of MDMA is needed. Second, research into the mechanisms of action of MDMA, which has strong mood-enhancing effects, will provide insight into the physiology of mood and pathophysiological processes involved in mood disorders. Third, normative data on the effects of MDMA in normals are useful to interpret results form studies in Ecstasy users. Forth, pharmacodynamics and pharmacokinetics of MDMA should be better characterized in the light of ongoing clinical phase II trials using similar doses of MDMA. The importance of these issues is recognized by researchers and regulatory authorities as demonstrated by the increase in number of approved controlled studies in humans.

Risk/benefit Ratio:Overall, the risk for severe adverse effects or lasting physical harm is considered very low. With regard to subjective distress, the overall effect of MDMA is clearly a pleasurable experience with comparatively minimal risks for dysphoric reactions and tolerable adverse effects. The potential risk of further abuse of MDMA is expected to be very low in healthy subjects with low risk of drug abuse liability such as previous significant drug use or preexisting psychiatric disorder. Taken together, the risks are minimal. Because healthy volunteers will participate in this phase I study, the benefits mainly consist in increased information that will not directly benefit the study participants but will be of benefit for the society and patients with Ecstasy intoxications. However, based on our experience with similar studies, subject mostly experienced pleasure and considered the use of MDMA in a controlled setting to be of some interesting and personal value.

## Ethical standards

The study will be performed in accordance with the Declaration of Helsinki, International Conference on Harmonization, Topic E6 Guidelines for Good Clinical Practice (GCP), the “Verordnung über klinische Versuche mit Heilmitteln” (VKlin), the “Heilmittelgesetz” (HMG), and standard operating procedures of the CRC/CTU of the University Hospital of Basel.

### Institutional Review Board

The PI will submit the study protocol and informed consent form to an approved IRB (institutional review board = Ethische Kommission beider Basel, EKBB).

### Protocol amendments

Any protocol amendments will require formal approval of the ethics committee prior to their implementation.

### Early study termination

The study may be ended early in the case of unexpected adverse events or other reasons based on the PIs decision and on criteria determined as outlined below.

- An interim analysis will be performed after 8 subjects have completed the study. If this analysis indicates a significant increase in measures that indicate increased monoamine release the study will be terminated early. Measures included in the analysis are: heart rate, blood pressure, the total of adverse effects (list of complaints), and adverse events.
- In addition, in the case of severe adverse events in a subject indicating excessive monoamine release, the code will be opened and results analyzed by the principal investigator. The following findings when due to MDMA and duloxetine administration will trigger early analysis of results and potential study termination:
  - Hypertension >Psys 200 mm Hg or Pdia 140 mm Hg
  - Tachykardia 120 beats/min
  - Serotonin syndrome (cloni, hyperthermia, delir)
  - Other unexpected severe adverse effects that could be linked to excessive release of monoamines

The PI will inform the IRB and Swissmedic when the study ends within 90 days or 15 days if the study is terminated early. A final report is sent to both within six months of study termination by the PI.

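### The interim safety stop in Protocol 14.4.3 leaves out body temperature, which is already recorded, and the blood-pressure figures in 14.4.3 and 14.2.6 are not tied together

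*Protocol*

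**What the plan says.** **Interim analysis.** Protocol 14.4.3 (Early study termination) states: "An interim analysis will be performed after 8 subjects have completed the study". A significant increase in measures of monoamine release ends the study. The list is closed: "Measures included in the analysis are: heart rate, blood pressure, the total of adverse effects (list of complaints), and adverse events".

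**Single-subject triggers.** The same section adds that "in the case of severe adverse events in a subject indicating excessive monoamine release, the code will be opened". Among the findings that qualify, when due to MDMA and duloxetine, is "Hypertension >Psys 200 mm Hg or Pdia 140 mm Hg". Serotonin syndrome is another, and hyperthermia is named as one of its features. Such findings "will trigger early analysis of results and potential study termination".

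**Subject-level rules.** Protocol 14.2.6 (Monitoring for specific toxicity) states: "Closer monitoring will be implemented if blood pressure values exceed 180/120 mm Hg". It goes on: "Treatment of a hypertensive reaction (Psys>220 mmHg) would include administration of oxygen", among other measures. It also has a temperature rule, which begins "If body temperature rises by more than 1.5" (°C) and leads to hydration and cooling.

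**Data collected.** Protocol 11.4.2.1 (Vital signs) records body temperature alongside blood pressure and heart rate, from 4 h before to 6 h after MDMA or placebo.

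**The concern.** The interim rule is the only planned group-level safety check, and its consequence is mandatory. What it can detect depends on its list. Protocol 7.1 attributes hyperthermic as well as hypertensive reactions to adrenergic activation, 14.2.6 gives hyperthermia its own rule, and 14.4.3 makes it part of a single-subject trigger. The group-level check nevertheless does not look at the temperature readings. Two of its four measures, blood pressure and heart rate, are the ones that secondary hypothesis 1 expects duloxetine to reduce. The other two pick up temperature only if somebody reports it.

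The second matter is the fit between 14.4.3 and 14.2.6. A pressure that 14.4.3 handles as a severe adverse event, with unblinding and review of the study, can lie below the only pressure at which 14.2.6 describes treatment. A reader at the bedside has two sections with different figures and no link between them.

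**Working it through.** **1. Temperature against the interim list.**

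| Place in the protocol | Temperature covered? |
|---|---|
| 11.4.2.1, vital signs | Yes: −4 h, 0, 20, 40, 60, 90, 120, 150, 180 min, 4, 5, 6 h (12 points, as for pressure and heart rate) |
| 14.2.6, toxicity rules | Yes: rise above 1.5 °C; also a 6 PM check against pretreatment |
| 14.4.3, single-subject triggers | Yes, as hyperthermia within serotonin syndrome, with no figure |
| 14.4.3, interim measures | Not named (0 of 4) |

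A moderate group shift can pass under the individual rule. Section 14.2.6 expects a rise of about 0.5 °C. If duloxetine added a further 0.5 °C (assumed), the mean rise would be 0.5 + 0.5 = 1.0 °C, below the 1.5 °C rule. It would reach the interim only if recorded as a complaint or adverse event.

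**2. Would 8 subjects be informative?** The protocol gives no SD for temperature, so a range is assumed. Inputs: n = 8 (14.4.3); paired t-test, df = 7, two-sided alpha 0.05, critical value 2.365; difference d = 0.5 °C (assumed). The noncentrality is d√n/SD = 0.5 × 2.828/SD.

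| Assumed SD of paired difference (°C) | Noncentrality | Power |
|---|---|---|
| 0.3 | 4.71 | 0.98 |
| 0.4 | 3.54 | 0.86 |
| 0.5 | 2.83 | 0.68 |
| 0.6 | 2.36 | 0.53 |

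**3. Cost in false stops.** With no true effect, a two-sided 0.05 test is significant in the direction of an increase with probability 0.05/2 = 0.025. The chance that at least one measure signals falsely therefore rises by at most 2.5 percentage points, and by less if temperature is correlated with the measures already listed.

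**4. Blood pressure, side by side.**

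| Step | Systolic (mmHg) | Diastolic (mmHg) | Section |
|---|---|---|---|
| Closer monitoring | 180 | 120 | 14.2.6 |
| Code opened, study review | 200 | 140 | 14.4.3 |
| Treatment of hypertensive reaction described | 220 | none given | 14.2.6 |

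The band above 200 and up to 220 is 220 − 200 = 20 mmHg wide. A reading of 210/110 falls in it. A reading of 190/145 meets the diastolic review trigger but no stated treatment value. Each rule can still be applied as written at either reading.

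**The case against.** **On blood pressure, most of the opposing case stands.** A reader might infer that the protocol contradicts itself, or that a subject sick enough to stop the trial goes untreated. The text supports neither.

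- The two sections do different jobs: one manages a subject, the other reviews the study. A review that starts below the treatment level is the cautious order, and 180/200/220 can be read as a graded ladder.
- The trigger leads to analysis and possible termination. It is not an automatic stop.
- Closer monitoring is not all that such a subject receives. Section 14.2.6 also requires watching for signs of hypertensive crisis, acts on angina at any pressure, and keeps subjects overnight on evening criteria. Section 14.2.3 provides appropriate treatment for anyone with an adverse event, with emergency care in house. Section 14 keeps subjects with severe reactions at the centre.

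What remains is that the protocol never presents the figures as a ladder, the diastolic column has no treatment entry, and neither section points to the other.

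**On temperature,** the list is a chosen set and its content contradicts nothing. Hyperthermia is covered for single subjects, and a temperature event recorded as an adverse event would enter the interim. It would be too strong to say that the protocol ignores temperature. It would also be too strong to predict that temperature will rise while blood pressure falls: section 7.1 reports that blocking norepinephrine effects reversed MDMA hyperthermia in rats, which suggests that the two might move together. The power figures rest on an assumed effect equal to the whole rise expected from MDMA. They show that the test could be useful, not that an effect is likely. None of this removes the gap: a group rise that is measured but not reported stays outside the interim.

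**Conclusion.** The omission of body temperature from the interim list is a real but modest weakness in a mandatory stopping rule. It is a gap in coverage, not an internal conflict. A test on 8 subjects would detect a 0.5 °C excess with probability between 0.53 and 0.98, given assumed SDs of 0.6 down to 0.3 °C. The calculation takes the relevant comparison to be duloxetine-MDMA against placebo-MDMA.

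The blood-pressure figures in 14.4.3 and 14.2.6 are compatible but unconnected. They leave a 20 mmHg systolic band, and the whole diastolic side, with a study-level step and no stated pressure-based treatment step. This calls for reconciliation. It does not show that any threshold is wrong.

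**What to change.** 1. In 14.4.3, add peak body temperature (duloxetine-MDMA against placebo-MDMA) to the interim measures. The readings are already collected and the analysis is already planned, so the cost is one line of protocol text and one more test. The downside is at most about 2.5 percentage points more chance of a false stop.
2. Have the sponsor reconcile 14.2.6 and 14.4.3 on systolic and diastolic pressure, and cross-reference the two sections. Which figures stand, and in what order, is the sponsor's clinical decision; no threshold or ordering is proposed here. The cost is protocol wording only.
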